### Randomization

After enrollment and a baseline assessment, patients will randomly be assigned by the study coordinator to the cognitive training group or the control group, which will not receive cognitive training. Patients will be randomized using a computer-generated randomization list with a 1:1 blocked allocation ratio. The randomization list will be sequentially numbered and will be generated by the study coordinator prior to the start of the study.

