## Methods

### Study design and enrollment

This study is a multicenter, randomized controlled trial conducted at the department of cardiac surgery of the Kerckhoff Heart and Thorax Center in Bad Nauheim, Germany, and at the department of cardiovascular surgery of the University Hospital Giessen, Germany. It complies with the Declaration of Helsinki and has been approved by the ethics committee of the Justus Liebig University Giessen (ref. 28/14). The study coordinator receives information about planned elective cardiac surgery from the participating study centers, which he screens according to eligibility criteria. Potential patients will be contacted and informed verbally and in writing in detail about the purpose, procedure, and possible consequences of the study project. If the patient agrees to participate, a written informed consent form will be signed by the patient and the investigator prior to the patient’s enrollment.

Our study team consists of members of the departments of neurology, neuropsychology, neuroradiology, heart surgery, and rehabilitation who are responsible for running the study, including preparing the protocol, monitoring the study and writing the study reports. The study protocol follows the SPIRIT (Standard Protocol Items: Recommendations for Interventional Trials) guideline (see Additional file 1).

Due to the planned small sample size, the expected lack of harm and the relatively short execution time of the cognitive training (3 weeks), the implementation of a data monitoring committee was not considered.

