### Blinding

Surgeons, radiologists and neuropsychologists who are involved in the outcome variables will be blinded to the randomization status. Cognitive testing and training will be carried out by two different, experienced neuropsychologists in order to maintain the blinding. During follow-up assessments, patients may tell the blinded neuropsychologist accidentally before the start of the neuropsychological test whether or not they have received previous cognitive training. In this case, however, the neuropsychological test will be performed and discussed in the study reports.

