### Power and sample size estimation

Cognitive training for patients undergoing heart surgery administered by de Tournay-Jette et al. (2012) [19] revealed medium-to-large effect sizes (*η*^2^ = 0.10–0.23). We have decided to use the smaller effect size (*η*^2^ = 0.10) for calculation so as not to underestimate the required sample size. Using this effect size, 37 patients per group are needed to obtain statistical power of 80% at a significance level of *p* = 0.05 (two-tailed). Based on previous cardiosurgical studies, we estimate a dropout rate of 20% between each of the four assessment time points. Thus, the number of study patients recruited at baseline assessment was fixed at 72 patients per group. For sample size and statistical power calculations, we used G*Power-3 analysis software.

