### Data management

All personal information about enrolled patients will be subject to medical confidentiality. Paper-based assessment forms will be used to record the outcome variables. The data will be manually entered in an electronic database, which is password-protected and will be checked for quality and accuracy. All assessment forms, signed informed consent forms, and the randomization list will be stored in a locked cabinet.

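### The study coordinator screens patients, writes the blocked randomization list and assigns from it, so allocation is not concealed from the person who assigns

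*Protocol article*

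**What the plan says.** Four sections of the protocol article bear on this.

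- **Study design and enrollment**, on screening: "The study coordinator receives information about planned elective cardiac surgery from the participating study centers, which he screens according to eligibility criteria". Consent is signed by the patient and the investigator; the section does not say that the coordinator obtains it.
- **Randomization**, on assignment: "After enrollment and a baseline assessment, patients will randomly be assigned by the study coordinator to the cognitive training group or the control group". On the method: "Patients will be randomized using a computer-generated randomization list with a 1:1 blocked allocation ratio". On the origin of the list: "The randomization list will be sequentially numbered and will be generated by the study coordinator prior to the start of the study". No block size is given.
- **Blinding**: "Surgeons, radiologists and neuropsychologists who are involved in the outcome variables will be blinded to the randomization status". The coordinator is not among those named.
- **Data management**: "All assessment forms, signed informed consent forms, and the randomization list will be stored in a locked cabinet".

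The legend of Fig. 1 places random assignment after the acute hospital stay, once the patient has moved to the rehabilitation center.

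**The concern.** Concealment means that whoever controls a patient's entry or place in the sequence cannot foresee the next assignment. Here the person who places patients in the sequence wrote the sequence.

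This matters more than usual in this trial. The control arm gets no placebo activity, so patients know their group, and much of the training is done alone in the ward room. Unpredictable allocation and blinded testers are the main protections. If the order of assignment could follow how well or how willing a patient seems after surgery, the arms could differ in motivation or frailty, and both plausibly affect test performance at discharge. The planned covariate analysis adjusts only for what was measured.

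**Working it through.** The point rests on who does what and when, so the check sets the sections side by side. The plan has no figure for concealment to reproduce.

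**Step 1: roles**

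| Task | Who | Section |
|---|---|---|
| Eligibility screening | Study coordinator | Study design and enrollment |
| Signing consent | Patient and investigator | Study design and enrollment |
| Generating the list | Study coordinator, before the study starts | Randomization |
| Assigning patients | Study coordinator | Randomization |
| Outcome testing | Blinded neuropsychologist, separate from the trainer | Blinding |

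Screening, list generation and assignment fall to one role.

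**Step 2: what can be foreseen, and when**

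- *At screening, before surgery.* The list exists, so its author can know the sequence. Slots are used only after transfer to rehabilitation, by patients from two centers and after any losses in between. The author therefore does not know which slot a given candidate will take. The exposure here is small.
- *At assignment, in rehabilitation.* The next slot is known, so 100% of upcoming assignments can be known to the list's author. By then intensive-care days, complications and delirium have been recorded (Study design and enrollment). If several patients are waiting, the order in which they take numbers can be influenced, as can whether a doubtful patient goes forward. This is the main exposure.

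On retention: the sample-size section expects 20% dropout between assessments. Between baseline and discharge that is 0.20 × 144 = 28.8, about 29 patients. Assignment falls inside this interval. The article does not say how many of these losses come before it.

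**Step 3: would a new list holder suffice if blocks stayed fixed?** Suppose the coordinator no longer sees the list but knows all past assignments and the block size. For block size b at 1:1, the expected share of assignments known with certainty is 1/(b/2 + 1). The block sizes below are assumptions.

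| b | Share certain |
|---|---|
| 2 | 1/2 = 50% |
| 4 | 1/3 = 33% |
| 6 | 1/4 = 25% |
| 8 | 1/5 = 20% |

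Moving the list takes the share from 100% to between 20% and 50%. Randomly varying block sizes are needed to reduce it further.

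**Step 4: how many patients could a change still reach?** Recruitment ran from 13 July 2016 and was due to end in February 2020, about 43 months. The protocol version is dated 10-08-2019. Even accrual is assumed.

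- Read as 10 August: about 37 months elapsed; (43 − 37)/43 × 144 = 20 patients, about 10 per arm.
- Read as 8 October: about 39 months elapsed; (43 − 39)/43 × 144 = 13 patients, about 7 per arm.

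The plan's own requirement is 37 evaluable patients per group for 80% power, so comparing results before and after the change would tell the reader nothing.

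**The case against.** The strongest reply has four parts.

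*Timing and limited discretion.* Patients are consented and tested at baseline before assignment, the eligibility criteria are mostly factual, and the investigator signs the consent. This stands. A reader might infer that the coordinator knows the next allocation when choosing whom to approach; the order of events does not support that. It does not remove the exposure at assignment.

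*Condensed article.* The full protocol may describe envelopes or another safeguard, so the article does not show that no such step exists. That is fair. But envelopes do not hide a list from its author, and the combination of roles is stated, not left out.

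*Baseline adjustment.* The analysis includes the baseline assessment, and the covariate analysis lists preoperative cognition, age, sex, education and depression or anxiety. This deals largely with measured imbalance. A reader might want to express the possible bias as a fraction of the assumed training effect. The document gives neither the share of places affected nor the difference between such patients, and a difference in baseline level is not the same as bias in change. No such figure is supported.

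*Storage.* A reader might infer from the Data management section that testers can easily see the list. The text says only that the cabinet is locked, not who can open it, and testing is separated from training. Shared storage is a reason for precaution, not evidence of unblinding.

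**Conclusion.** The concern holds in a limited form. One role screens, writes the list and assigns, so allocation is not concealed from the person who assigns. The exposure is mainly the order, timing or retention of patients already enrolled and, to a lesser degree, whom to approach. At assignment, foreknowledge can be complete; the size of any bias is unknown. Nothing in the document suggests that anyone acted on such knowledge.

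The conclusion rests on two readings: that the study coordinator named in both sections is the same role, and that assignment takes place where the Fig. 1 legend puts it. It should be fixed for the remaining patients and disclosed for the others. It does not by itself invalidate the trial.

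**What to change.** For all patients not yet assigned:

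1. Have an existing team member with no role in screening, consent, training or testing generate a new list with randomly varying block sizes and hold it.
2. Release each assignment, for example by sealed opaque envelope or telephone, only after consent, baseline testing and arrival in rehabilitation.
3. Keep the list apart from the assessment forms, as a precaution for tester blinding.
4. In the report, give the number of patients assigned under each procedure and state the earlier lack of concealment as a limitation. Do not repeat the primary analysis by procedure.

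The cost is a short amendment and some time from existing staff; sample size, outcomes and training are unchanged. The downside is a small change of procedure in mid-trial that may reach only a minority of patients, which makes the disclosure in item 4 the more important part.

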### Blinding

Surgeons, radiologists and neuropsychologists who are involved in the outcome variables will be blinded to the randomization status. Cognitive testing and training will be carried out by two different, experienced neuropsychologists in order to maintain the blinding. During follow-up assessments, patients may tell the blinded neuropsychologist accidentally before the start of the neuropsychological test whether or not they have received previous cognitive training. In this case, however, the neuropsychological test will be performed and discussed in the study reports.

### Neuropsychological assessment

A battery of cognitive tests will be performed by a neuropsychologist on the day before surgery, at discharge from rehabilitation, and at 3 and 12 months after discharge. When available, parallel test forms will be used at follow up to account for learning effects. The order in which the parallel test forms are presented will be counterbalanced so that each parallel test form occurs with the same frequency at each test time point.

The cognitive test battery assesses selective attention, verbal and visual memory with short-delay and long-delay episodic memory conditions, verbal working memory, cognitive flexibility, word fluency and symbol processing. Selective attention will be examined using the Trail Making Test A (TMT-A) [20] and the *Alterskonzentrationstest* (AKT) [21]. In the TMT-A, the patient has to link numbers in ascending order on a test sheet. The AKT consists of a matrix of similar visual stimuli, where a target stimulus has to be marked.

To assess verbal memory, the *Verbaler Lern- und Merkfähigkeitstest* (VLMT), a modified German version of the Rey Auditory Verbal Learning Test [22], will be applied. This test can be used to evaluate short-term memory, learning, episodic memory, and verbal discriminability. First, the patient has to concentrate on a word list that is read out loud by the investigator. The direct retrieval of the patient is scored as short-term memory performance. Second, the patient has to learn the word list in five learning trials. The sum of the recalled words represents a learning parameter. Third, a second word list with new words is presented verbally only once, to divert attention from the first word list. After this, the learned words of the first word list have to be recalled; this is used as a measurement of a short-delayed function of verbal episodic memory. A second verbal episodic memory measurement is performed 20 min later (long delay). Finally, the verbal recognition ability is proven by discriminating between already learned and new words. Between the short-delayed verbal episodic memory trial and the long-delayed verbal episodic memory trial, nonverbal cognitive tests are performed to avoid the potential effect of interfering words not included in the learned wordlist.

Visual memory will be examined using the Block-Tapping Test [23], the Non-Verbal Learning Test (NVLT) [24] and the pictorial memory subtest of the German *Syndrom-Kurztest* (SKT) [25]. In the Block-Tapping Test, the patient has to tap blocks on a board with his or her hand in a given order forward and backward. The NVLT is a test to evaluate the visual recognition of repeated abstract symbols within a variety of 60 cards. The pictorial memory subtest of the German SKT will be administered to the patient to evaluate short-term episodic memory and recognition of 12 visual pictures, which are presented in one learning trial. With the Letter Number Test, a subtest of the MATRIX test battery, the verbal working memory is tested through the mental reorganization of numbers and letters [26]. Cognitive flexibility will be assessed by the Trail Making Test B (TMT-B) [20], where numbers and letters have to be alternately linked, and by another subtest of the SKT (SKT 7) [25], where the patient has to name interfering letters (e.g., “A” instead of “B,” and vice versa).

Furthermore, semantic and phonetic verbal fluency will be tested using the “Regensburger Wortflüssigkeits-Test” (RWT) [27]. In this test, in 1 min, the patient has to name words from a specific category to test semantic fluency and words with a specific initial letter to test phonetic fluency. At the end of the test battery, the *Symbolverarbeitungstest* (SVT) will be performed to test the processing of symbolic pictures [28].

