### Planned statistical analyses

The effect of cognitive training will be analyzed by repeated measures (mixed between-within) analysis of variance (ANOVA) with groups (control group/intervention group) as the between-subject factor and assessment time (baseline and all follow-up assessments) as the within-subject factor for all cognitive tests and questionnaires, respectively. Assumptions for repeated measures ANOVA will be tested using the Levene test for variance-homogeneity and Mauchly’s test for sphericity. If sphericity is violated, alpha levels will be adjusted using the Greenhouse-Geisser correction. Normal distribution will be tested using the Shapiro-Wilk test. To control for the possibility of confounder variables that could affect the results, we will conduct additional repeated measures analysis of covariance (ANCOVA), which includes covariates such as preoperative cognitive values, age, sex, education, psychiatric scores (depression/anxiety), and perioperative variables such as duration of extracorporeal circulation, administration of anesthesia, and number and size of ischemic lesions.

Post hoc explorative between-subject comparisons will be analyzed using the *t* test for independent samples. In this case, we will compare the intervention group with the control group by calculating a change score in cognitive values (post-training score minus pre-training score). The change in cognitive values is the dependent variable, and the treatment group (cognitive training group/control group) is the independent variable.

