Within-subject comparisons will be analyzed using the paired *t* test. When the assumptions for parametric tests (normal distribution, variance-homogeneity between two groups) are not given, the variables will be analyzed using non-parametric variance techniques. In this case, between-group differences will be calculated using the Mann-Whitney U test, using change scores in cognitive values (post-training score minus pre-training score) and the Wilcoxon signed-rank test for within-group comparisons. Nominal variables will be analyzed by Pearson’s chi-squared test. Depending on the parametric level of the data, correlation with continuous variables will be calculated using Pearson product-moment correlation, Spearman rank correlation, or Kendall tau correlation. Effect size of the cognitive training will be calculated by the difference in the pretest-posttest measure between the intervention and control group, weighted by the pooled standard deviation of the pretest measurement, because this is the recommended choice for a pretest-posttest controlled design [38]. The criterion for statistical significance will be set at *p* < 0.05. In the case of multiple tests, we will control *p* values using the false discovery rate (FDR) correction method [39]. Since we expect dropout of some patients on follow-up assessments, all patients will be included in the intention-to-treat analysis, where missing data will be imputed by a multiple imputation method. To evaluate the impact of missing data, a complete case analysis will also be performed, followed by best-worst and worst-best case sensitivity analyses.

Another approach to identifying a training effect on cognition will be to compare the frequencies of POCD and POCI between the groups using Pearson’s chi-squared test. POCD will be defined as a decline from pre to post assessment of 1 standard deviation in at least two neuropsychological parameters as this is a widely used method [2]. Similarly, POCI will be defined as an improvement from pre to post assessment of 1 standard deviation in at least two neuropsychological parameters.

Interim analyses will be carried out during the study period to identify adverse events, an overwhelming effect, or the futility of the experimental arm. In this case, the study could be terminated prior to its completion. The decision will be made by the study team.

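### The parallel test forms are counterbalanced, but no stated analysis includes the form, so any difference in form difficulty costs precision and blurs individual POCD/POCI labels without biasing the arm comparison

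*Protocol article*

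**What the plan says.** **Forms.** Under Neuropsychological assessment, the protocol article states: "When available, parallel test forms will be used at follow up to account for learning effects". Their order is "counterbalanced so that each parallel test form occurs with the same frequency at each test time point". So at any visit different patients may sit different forms of the same test. The article does not say which tests have parallel forms, how many forms there are, or whether they are equally difficult.

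**Allocation.** The Randomization section describes a "computer-generated randomization list with a 1:1 blocked allocation ratio". It does not mention form order.

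**Models.** Planned statistical analyses sets up a repeated measures ANOVA "with groups (control group/intervention group) as the between-subject factor and assessment time (baseline and all follow-up assessments) as the within-subject factor". An additional ANCOVA, aimed at confounders, is one "which includes covariates such as preoperative cognitive values, age, sex, education, psychiatric scores (depression/anxiety") and perioperative variables. Exploratory comparisons between arms use a t test or Mann-Whitney test on raw change scores.

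**Labels.** "POCD will be defined as a decline from pre to post assessment of 1 standard deviation in at least two neuropsychological parameters". POCI is the mirror image, and the frequencies of both are compared between arms by chi-squared test. No step adjusts for the form used.

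**The concern.** Counterbalancing makes sense only if the forms might differ. It equalises the average difficulty at each visit, but it does not remove the difference from one patient's change. If one form is harder, patients who meet it second seem to lose ground and patients who meet it first seem to gain. In a model with group and time only, this variation goes into the error term, although it comes from a design factor that could be modelled.

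The 1-SD rule is more exposed because it acts on single patients. Whether someone is called declined or improved would depend partly on the form order assigned. At stake are some power in the primary comparison at discharge and the meaning of a POCD or POCI label for the individual.

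**Working it through.** **1. The plan's own sample size.** Inputs from Power and sample size estimation: η² = 0.10, power 80%, two-sided 0.05, 20% dropout in each of three intervals.

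- f = √(0.10/0.90) = 0.333, so d = 2f = 0.667.
- The noncentral t distribution gives 37 per group (power 0.808), as stated.
- 37/0.8³ = 72.3, against 72 stated.

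The plan's figures reproduce. The 37 per group is the number left after three intervals, at 12 months. At discharge one interval has passed: 72 × 0.8 = 57.6, so about 57 per group. With no form effect, power there is 0.94.

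**2. Change variance.** Assumed, because the documents do not give them: two forms, half the patients in each order, retest correlation r = 0.7, forms differing by δ baseline SD. The design effect size is taken to contain no form variance.

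- Without a form effect, the variance of change is 2(1 − r) = 0.6 SD².
- Form order shifts each change by +δ or −δ, which adds δ².
- The inflation is therefore δ²/0.6, and the standardised effect becomes 0.667/√(1 + δ²/0.6).

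| δ (SD) | Variance increase | Effect | Power, 57 per group | Power, 37 per group |
|---|---|---|---|---|
| 0 | 0% | 0.667 | 0.94 | 0.81 |
| 0.2 | 0.04/0.6 = 7% | 0.645 | 0.93 | 0.78 |
| 0.3 | 0.09/0.6 = 15% | 0.622 | 0.91 | 0.75 |
| 0.5 | 0.25/0.6 = 42% | 0.560 | 0.84 | 0.66 |

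Over r = 0.5 to 0.8 and δ = 0.2 to 0.5, power at 57 per group runs from 0.93 down to 0.79.

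**3. A 1-SD decline on one test, with no true change.** The SD of change is √0.6 = 0.775. The unit is taken as the baseline SD, which the article does not specify.

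- Equal forms: Φ(−1/0.775) = 9.8%.
- δ = 0.3, harder form second: Φ(−0.7/0.775) = 18.3%.
- δ = 0.3, easier form second: Φ(−1.3/0.775) = 4.7%.
- Average over both orders: (18.3 + 4.7)/2 = 11.5%.

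**4. The rule of at least two parameters, and the arm comparison.** Simulation: 4,000 runs, 57 per group, 15 parameters of which 7 have forms (with the same order on all seven), correlation of 0.3 between tests, r = 0.7, no true change. All of these are assumptions.

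- False POCD is 35% with equal forms. At δ = 0.3 it is 37% overall: 48% in one form order and 27% in the other.
- For δ from 0 to 0.5, the mean difference between arms stays between −0.002 and 0.006 SD. The type I error is 0.048 to 0.051 for the t test and 0.047 to 0.052 for the chi-squared test.

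**5. How well the form difference can be estimated (r = 0.7).**

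- From baseline alone, 72 patients per form: SE = √(2/72) = 0.17 SD.
- From within-patient changes pooled over arms, about 57 patients per order: SE = ½ × √(0.6 × 2/57) = 0.07 SD.

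**The case against.** The case against is substantial, and most of it stands.

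- **No bias.** A reader might infer that form differences pass for a training effect. The documents do not support that: form order is counterbalanced, arms are randomized, and the simulation shows neither bias nor excess type I error. That balance within arm is not mentioned does not change this, because ordinary standard errors cover chance imbalance.
- **An article is condensed.** A reader might infer that form will never enter the analysis. That cannot be shown: the covariate list is open, and a fuller plan may hold more. But the open list belongs to the additional confounder ANCOVA. The main model, the change-score tests and the POCD/POCI rule are each stated, and none names form.
- **The size is assumed.** Nothing in the article says that any forms differ, and tests without parallel forms are untouched. This stands in full.
- **The comparison at discharge has power to spare.** It would be wrong to discount 37 per group there, since about 57 are expected. At r = 0.7, power stays above 80% throughout. Only the extreme corner (r = 0.8, δ = 0.5) falls just below, at 0.79.
- **POCD/POCI is a supplementary approach, and its overall rate hardly moves** (35% to 37%). True, but who receives the label changes more than how many do.
- **A correction could add noise.** An adjustment from baseline scores alone, with 95% limits of about ±0.33 SD, would be as uncertain as the effect it removes. The pooled within-patient estimate is much better, at 0.07 SD.

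**Conclusion.** The point holds as a minor one about precision and classification. For tests with parallel forms, the stated analyses leave any difference in form difficulty in the error of the change scores and in individual POCD/POCI labels. The misclassification is the same in both arms in expectation, so it weakens the comparison without tilting it.

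Under the assumptions of two forms, r = 0.7 and a difference of 0.2 to 0.5 SD, the cost at discharge is between about 1 and 10 percentage points of power (0.94 to 0.93, 0.91 or 0.84). The individual label is affected more. At 0.3 SD, an unchanged patient's chance of a 1-SD decline on one test is 18.3% or 4.7% depending on form order. If the forms are equivalent, all of this vanishes. Nothing here calls the validity of the primary test into question.

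**What to change.** 1. For each test with parallel forms, add form or form order as a factor in the discharge comparison and in the repeated measures models. In a group-by-time ANOVA, form order must enter with its interaction with time, because a main effect of order alone leaves the difference in the changes.
2. Report POCD and POCI on form-adjusted scores, at least as a sensitivity analysis beside the raw rule. Estimate the form effect from the within-patient model pooled over both arms, not from baseline scores alone.
3. State which tests have parallel forms, and confirm that the form used is recorded for each patient and visit. Counterbalancing implies that such a schedule exists.

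Re-balancing form order within arm is not worth pursuing: the randomization list was generated before the study began, and chance imbalance is already covered by the standard errors.

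Cost: a few degrees of freedom per affected test and, if the forms are truly equivalent, slight added noise in the adjusted labels. No extra visits or tests are needed. If the forms do differ, power at 57 per group returns to about 0.94 under the assumptions above.
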